## Obtaining permission to conduct the study at the medical institution

The chief principal investigator will listen to the opinion of the certified review board and obtain approval from the administrators of each participating medical institution regarding whether the study can be carried out at the particular institution, before submitting the implementation plan to the Minister of Health, Labour and Welfare.

# **Statistical analysis**

## Sample size

100 cases (Finerenone group, 50 cases; placebo group, 50 cases)

Rationale for sample size determination

During the research plan formulation, the clinical evidence on the effects of finerenone on surrogate markers, including vascular stiffness and biomarkers in patients with CKD complicated by type 2 diabetes, was limited. Therefore, the study sample size was set based on the results of two clinical trials: one that examined the effects of a drug of the same type as finerenone on these surrogate markers and another that examined the effects of a drug of a different type on surrogate markers similar to those in this study.

　First, a clinical trial using eplerenone, a different MRA, reported in 2021 (MIRAD: Mineralocorticoid Receptor Antagonists in Type 2 Diabetes) (1) revealed that administration of eplerenone for 26 weeks significantly improved the levels of surrogate markers associated with heart disease in patients with type 2 diabetes compared to that by placebo. The total number of participants analyzed in the study was 104, and although the participants and endpoints were different from those in this study, the effectiveness of MRA on surrogate markers related to cardiac and renal disease may be verified with a similar number of cases.

　Next, in a subanalysis of the EMPA-TROPISM trial assessing patients with HFrEF (2), after six months of administration of the SGLT2 inhibitor empagliflozin, the change in vascular stiffness assessed by aortic pulse wave velocity was –0.58 cm/s (–0.36 SD) in the empagliflozin group and +0.60 cm/s (+0.60 SD) in the placebo group, demonstrating a significant improvement with empagliflozin (estimated effect size is approximately –0.36 SD–0.60 SD = –0.96 SD), and at the same time, proteomic analysis revealed a reduction in some inflammatory biomarkers. Moreover, in the PROTECT trial (jRCT1071220089) assessing patients with type 2 diabetes, although not limited to patients with CKD, the average CAVI value was approximately 9 with an SD of approximately 1.5 (unpublished data). Using these values, –0.6SD approximately yields a CAVI of –1; thus, in this study, the CAVI value of approximately 9 is expected to lower by approximately 1. In studies focusing on patients with diabetes and the general population (3,4), the CAVI value increased by 0.5 with approximately 10 years of aging; thus, lowering the CAVI by 1 point is equivalent to delaying the progression of arterial stiffness by approximately 20 years, and is considered to be clinically significant.

　Although no studies have directly compared the clinical effects of finerenone and empagliflozin, based on previous studies, if we assume that finerenone will improve vascular stiffness similar to that by empagliflozin as observed in the EMPA-TROPISM trial, we conservatively estimated that the CAVI in SD units from baseline to 24 weeks after treatment initiation would be reduced by > –0.6 (63% of the effect detected in the EMPA-TROPISM trial, calculated as –0.96 × 0.63 = –0.6) in the finerenone group compared to that in the placebo group, and set the significance level at 5% on both sides, power at 80%, and dropout rate at 10%. Thus, the minimum number of cases required to detect a significant difference between the two groups was set at 100 (50 in each group).

References:

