## **Analysis of the primary endpoint**

The following analysis will be performed on the FAS as the primary analysis. Furthermore, an analysis will be conducted using the PPS to confirm the robustness of the results.

1. Descriptive statistics calculations will be conducted, and histograms will be plotted to assess CAVI and its participant-level change and proportional change by treatment group and study visit. Inferential statistics calculations will be used to estimate CAVI mean and change, and geometric mean and proportional change at population-level by treatment group and study visit.
2. As the primary analysis for the primary endpoint, change in CAVI at 24 weeks will be analyzed using a linear regression model with baseline values as covariates and allocation as fixed effects. To assess treatment effect, the between-group difference in CAVI change using the least squares mean at 24 weeks will be estimated using the placebo group as a reference. The output will be the *P* value of the test for the null hypothesis that the between-group difference in change is 0. Moreover, the presence or absence of a treatment effect will be determined using the criteria of a two-sided *P* value of < 0.05.
3. As a supplementary analysis for the primary endpoint, change in logarithmic CAVI at 24 weeks will be analyzed using a linear regression model with logarithmic baseline values as covariates and allocation as fixed effects. To assess treatment effect, the between-group ratio of the proportional change in CAVI geometric mean using the least squares mean at 24 weeks will be estimated using the placebo group as a reference. The output will be the *P* value of the test for the null hypothesis that the between-group ratio is 1.

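### The source effect of -0.96 SD adds two changes standardized by different SDs (about -0.88 on a pooled SD), and the step from 0.6 SD to about 1 CAVI point does not say which SD is meant

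*Combined protocol and SAP*

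**What the plan says.** The protocol's section on sample size starts from a substudy of an empagliflozin trial in heart failure, with aortic pulse wave velocity as outcome. The change over six months is given as minus "0.58 cm/s (–0.36 SD) in the empagliflozin group" and plus "0.60 cm/s (+0.60 SD) in the placebo group". The section combines them: "estimated effect size is approximately –0.36 SD–0.60 SD = –0.96 SD". It then takes a discounted value for finerenone, "calculated as –0.96 × 0.63 = –0.6", describes it as conservative, and says that it "set the significance level at 5% on both sides, power at 80%, and dropout rate at 10"%. The result is 50 patients per group, 100 in all.

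The same section translates the planning effect into CAVI points. From another trial in type 2 diabetes it reports that "the average CAVI value was approximately 9 with an SD of approximately 1.5 (unpublished data"), and concludes that minus "0.6SD approximately yields a CAVI of –1". It equates 1 point with about 20 years of arterial ageing, at 0.5 points per 10 years, and regards that as clinically significant.

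The primary analysis in the SAP (Analysis of the primary endpoint, item 2) models the 24-week change in CAVI with a "linear regression model with baseline values as covariates and allocation as fixed effects". The protocol's efficacy analysis section specifies the same model. Neither document gives an SD of the change in CAVI or a correlation between baseline and week 24.

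**The concern.** There are two separate weaknesses in the chain from source trial to design.

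First, a change in SD units is a raw change divided by an SD. Two such values can be added or subtracted only if the SD is the same. Here each raw change is printed next to its SD-unit value, and the implied SDs differ by a factor of 1.6. The sum is therefore not a standardized difference between arms on any single SD.

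Second, the 0.6 comes from standardized changes, but it is converted to CAVI points with the SD of CAVI values between patients. The precision of the planned baseline-adjusted analysis depends on the residual SD after adjustment, which is a different quantity.

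At stake is what the rationale can be cited for: how conservative 0.6 SD is relative to the source trial, and whether the trial was sized around a 1-point CAVI difference.

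**Working it through.** **Inputs from the protocol's sample size section:** changes -0.58 (= -0.36 SD) and +0.60 (= +0.60 SD); planning effect 0.6 SD; two-sided alpha 5%; power 80%; dropout 10%; CAVI SD about 1.5; ageing 0.5 points per 10 years. Allocation is 1:1 (Randomization procedure). **Assumed, not in the documents:** equal arm sizes in the source trial, SD 1.5 at both visits, and a baseline to week-24 correlation r between 0.5 and 0.9.

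**1. The plan's own figure.** A two-sample t-test at d = 0.6 with 80% power needs 45 per arm. 45/0.9 = 50 per arm, total 100. Power with 45 evaluable per arm is 80.4% (81.2% by the normal approximation). The stated N and power reproduce.

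**2. The source effect on one scale.**
- Implied SDs: 0.58/0.36 = 1.61 and 0.60/0.60 = 1.00
- Pooled SD: √[(1.61² + 1.00²)/2] = 1.34
- Raw difference: 0.58 + 0.60 = 1.18
- Standardized: 1.18/1.34 = 0.88

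Rounding in the printed SD units moves this only between 0.87 and 0.89. The stated 0.96 is about 9% higher (0.96/0.88 = 1.09).

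**3. Consequence for the planning effect.**

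| What is held fixed | d | Share of 0.88 | Power, 45 per arm (t) |
|---|---|---|---|
| The 0.6 SD | 0.60 | 0.6/0.88 = 68% | 80.4% |
| The 63% discount | 0.63 × 0.88 = 0.55 | 63% | 73.9% |

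In the second row, 80% power would need 53 evaluable per arm, and 53/0.9 gives 59 randomized per arm.

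**4. The CAVI conversion on its own terms.** 0.6 × 1.5 = 0.9 points. At 0.05 points per year that is 0.9/0.05 = 18 years, against 1/0.05 = 20. A full point would be 1/1.5 = 0.67 SD.

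**5. What 0.6 SD means in CAVI points under each possible SD.** SD of change = 1.5√[2(1 − r)]; residual SD after baseline adjustment = 1.5√(1 − r²). Each SD is multiplied by 0.6. With 45 per arm, 0.6 residual SD is close to the difference detectable with 80% power in the planned model.

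| r | 0.6 × SD of values | 0.6 × SD of change | Residual SD | 0.6 × residual SD |
|---|---|---|---|---|
| 0.5 | 0.90 | 0.90 | 1.30 | 0.78 |
| 0.7 | 0.90 | 0.70 | 1.07 | 0.64 |
| 0.8 | 0.90 | 0.57 | 0.90 | 0.54 |
| 0.9 | 0.90 | 0.40 | 0.65 | 0.39 |

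Conversely, if 1.5 is the intended SD and the true difference is 0.9 points, the baseline-adjusted analysis has about 90% power at r = 0.5 and 97.6% at r = 0.7.

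**The case against.** The strongest reply is that the sample size rests on 0.6 SD and nothing else. Once 0.6 is chosen, neither 0.96 nor 1.5 enters the calculation, and N = 100 with 80% power reproduces. The 63% may simply describe the choice: 0.6/0.96 is 62.5%. Against 0.88, 0.6 is still a discount of about a third. This stands. A reader might infer from the addition error that the trial is underpowered or that its 80% does not follow; the documents do not support that. The 74% applies only if the discount, rather than the 0.6, is taken as the planning rule.

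Next, 0.88 depends on a convention. Dividing 1.18 by the empagliflozin-arm SD gives 0.73, and by the placebo-arm SD 1.18, so 0.96 lies between them. With 63% of each, power runs from 58% to 94%. This stands as a caution about precision. It does not rescue 0.96, which is not the raw difference over either arm's SD or their pooled SD.

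Third, a reader might conclude that the conversion uses the wrong SD. The protocol never says whether 0.6 is in units of CAVI values or of change. If it is values, 1.5 is consistent and the adjusted analysis has more power than stated. The supportable criticism is an undefined SD. Rounding 0.9 to 1 is also flagged as approximate in the text.

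Finally, a reader might infer that a significant result would be clinically trivial. That depends on correlations that the documents do not give. The SAP uses P < 0.05 only to decide whether an effect is present, and the protocol requires the difference with its 95% confidence interval. Reading that interval against 1 point is an option, not a missing requirement.

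**Conclusion.** The point holds as a fault in the derivation, not in the sample size. The source effect should read about -0.88 SD (0.87 to 0.89 with rounding, equal arms and pooled SD assumed) rather than -0.96. N = 100 and 80% power stand for an assumed 0.6 SD. What changes is the justification: 0.6 is 68% of the source effect, or, if 63% is kept, d is 0.55 and power about 74%.

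The 1-point CAVI target is not established. On the protocol's own terms it is 0.9 points, or 18 years of ageing. On any other reading it depends on an SD that is not defined and a correlation that is not given. That the detectable difference lies far below 1 point cannot be asserted from the documents; with SD 1.5 at both visits it would be 0.78 points at r = 0.5 and 0.39 at r = 0.9.

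**What to change.** Keep N = 100 and amend the sample size rationale, with matching wording in the report:

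1. Give the source effect as about -0.88 SD, naming the pooled SD and the equal-arms assumption.
2. State one of two things: that 0.6 SD is a chosen value equal to 68% of the source effect (power 80%), or that the 63% discount is kept (d about 0.55, power about 74%).
3. Say which SD the 0.6 refers to: CAVI values, change in CAVI, or the residual after baseline adjustment.
4. Replace the 1-point figure. If 1.5 is the intended SD, write 0.9 points and 18 years. Otherwise give the difference detectable with 80% power under the baseline-adjusted model, with the assumed correlation and a range such as that in the table above.

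This costs wording only: no extra patients and no change to the analysis or the decision rule. The downside is that the stated justification looks slightly less favourable.

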# Analysis set

# Efficacy analysis set

# Full analysis set (FAS)

In accordance with the intention-to-treat principle, the FAS, excluding the following cases, will be used for efficacy analysis:

- - Patients who withdrew consent after enrollment
  - Patients identified to be ineligible after enrollment
  - Patients not administered protocol treatment after allocation
  - Patients with no data on efficacy after protocol treatment initiation

## Per-protocol set (PPS)

Among the FAS, the patient population without any significant deviations from the study plan will be designated as the PPS and will be used for supplementary efficacy analysis.

The data center will evaluate deviations from the study plan as cases accumulate, and before the study data is finalized, a case review meeting will be held with the principal investigator, the head of statistical analysis, the data center, and monitoring staff to define and extract cases of significant deviations from the study plan.

### Safety set (SS)

Randomized patients administered at least one dose of protocol treatment will be included in the safety set (SS).

## Analysis method

For assessing efficacy, FAS will be used as the primary analysis population with supplementary analysis of the PPS for sensitivity analysis. The significance level for all statistical tests will be two-sided at 0.05. No adjustment for multiplicity of tests will be conducted except for proteomics analysis. For details of the analysis not described in this research plan and abnormal data including outliers, the handling method will be considered before conducting the statistical analysis, and a statistical analysis plan will be created and established before the data is finalized. If any changes to the statistical analysis plan results in a consequent change in the research plan, the research and statistical analysis plans will be revised, and the details of the revisions will be explained in the overall report of the study.

## Case composition

A flow diagram will be created for cases with obtained consent, cases not enrolled, cases enrolled/allocated, cases discontinued, cases completed, and cases for which primary endpoints can be analyzed.

## Description of analysis set

The number of cases will be listed for each FAS, PPS, and SS. Excluded cases will be tabulated by the reasons for exclusion, and a list of excluded cases will be created.

## Patient background and baseline values

For patient characteristics in the FAS, summary statistics (number of cases, mean, standard deviation, minimum, 1st quartile [Q1: 25th percentile], median, 3rd quartile [Q3: 75th percentile], maximum) will be calculated for quantitative variables, and the number of cases and percentages (%) will be calculated for qualitative variables by treatment group. Furthermore, the number of cases and percentages (%) will be obtained for complications and use of prior medications by treatment group.

## Efficacy analysis

## Efficacy analysis

1. Analysis of the primary endpoint

The change in CAVI at 24 weeks after protocol treatment initiation compared to that at baseline will be analyzed using a linear regression model with the treatment group as a fixed effect factor and baseline CAVI value as a covariate. Moreover, the mean values of both treatment groups at 24 weeks and their 95% confidence intervals, as well as the treatment effect estimated by the difference in the mean values between the treatment groups and their 95% confidence intervals will be calculated. A test will be performed against the null hypothesis such that the difference in treatment effect is 0.

1. Analysis of secondary endpoints
2. Proportional change in geometric mean of UACR at 12 and 24 weeks after protocol treatment initiation compared to that at baseline (important secondary endpoint):

The change in logarithmic UACR values from baseline to 12 and 24 weeks after the protocol treatment initiation will be analyzed using mixed-effects models for repeated measures (MMRM) with the treatment group as a fixed effect factor, baseline value and time point as covariates, and group and time point interaction. The results will be back-transformed to the original UACR scale, and the proportional change in UACR geometric mean and its 95% confidence interval for both treatment groups at 12 and 24 weeks, as well as the treatment effect estimated by the ratio of the proportional change between the treatment groups and its 95% confidence interval, will be calculated. A test will be performed against the null hypothesis such that the treatment effect ratio is 1 at each time point.

1. Proportional change in geometric mean of blood biomarkers (pentosidine) and urinary biomarkers (type IV collagen, α1-MG, β2-MG, NGAL, NAG, L-FABP creatinine ratio) at 24 weeks after the protocol treatment initiation as compared to those at baseline:

The change in logarithmic value of each blood biomarker from baseline to 24 weeks after the protocol treatment initiation will be analyzed using a linear regression model with the treatment group as a fixed effect factor and the baseline value as a covariate. The results will be back-transformed to the original scale, and the proportional change in the geometric mean of both treatment groups at 24 weeks and its 95% confidence interval, as well as the treatment effect estimated by the ratio of the proportional change between the treatment groups and its 95% confidence interval, will be calculated. A test will be performed against the null hypothesis such that the treatment effect ratio is 1.

1. Analysis of other endpoints
2. Changes from baseline in vital signs, including weight, BMI, eEV, blood pressure, pulse pressure, and pulse rate in the clinic, and blood pressure, pulse pressure, and pulse rate at home at 4, 12, and 24 weeks after protocol treatment initiation:

The change from baseline in each outcome at each time point after the protocol treatment will be analyzed using MMRM with the treatment group as a fixed effect factor, baseline value and time point as covariates, and group and time point interaction, to calculate the mean values of both treatment groups at each time point and their 95% confidence intervals, as well as the treatment effect estimated by the difference in the mean values between the treatment groups and their 95% confidence intervals. A test will be performed against the null hypothesis such that the treatment effect difference is 0.

1. Changes from baseline in blood test indices, including serum creatinine, eGFR, serum cystatin C*, serum potassium, HbA1c*, plasma aldosterone concentration**, plasma renin activity** at 4, 12, and 24 weeks after the protocol treatment initiation (*Evaluated only at baseline, and 12, and 24 weeks, **Evaluated only at baseline and 24 weeks):

The change from baseline in each outcome at each time point after protocol treatment initiation will be analyzed using a linear regression model with the treatment group as a fixed effect factor and the baseline value as a covariate, or MMRM with the treatment group as a fixed effect factor, the baseline value and time point as covariates, and the interaction between group and time point. The mean values of both treatment groups at each time point and their 95% confidence intervals, as well as the treatment effect estimated by the difference in the mean values between the treatment groups and their 95% confidence intervals, will be calculated. A test will be performed against the null hypothesis such that the difference in treatment effect is 0. If the distribution of values deviates significantly from a normal distribution, appropriate scale transformation will be performed as necessary.

1. Changes from baseline in AI and % mean arterial pressure at 24 weeks after protocol treatment initiation:

The change from baseline in each outcome at 24 weeks after the protocol treatment initiation will be analyzed using a linear regression model with the treatment group as a fixed effect factor and the baseline value as a covariate. Moreover, the mean values of both treatment groups at 24 weeks and their 95% confidence intervals, as well as the treatment effect estimated by the difference in the mean values between the treatment groups and their 95% confidence intervals will be calculated. A test will be performed against the null hypothesis such that the difference in treatment effect is 0. If the distribution of values deviates significantly from a normal distribution, appropriate scale conversion will be performed as appropriate.

1. Changes from baseline in cardiac function indices, including LVEF, septal e′, lateral e′, E, E/e′*, LVMI, LAD, and LAVI assessed by echocardiography 24 weeks after protocol treatment initiation, compared to those at baseline:

The change from baseline in each outcome at 24 weeks after the protocol treatment initiation will be analyzed using a linear regression model with the treatment group as a fixed effect factor and the baseline value as a covariate. Moreover, the mean values of both treatment groups at 24 weeks and their 95% confidence intervals, as well as the treatment effect estimated by the difference in the mean values between the treatment groups and their 95% confidence intervals will be calculated. A test will be performed against the null hypothesis such that the difference in treatment effect is 0. If the distribution of values deviates significantly from a normal distribution, appropriate scale conversion will be performed.

1. Changes in abundance of up to 181 proteins comprehensively analyzed by proteomic analysis (Target 96 panel) at 24 weeks after protocol treatment initiation as compared to that at baseline (exploratory endpoint):

Comprehensive comparisons between groups will be performed for each evaluation item using *t*-tests. The Benjamini–Hochberg method will be used to control the false discovery rate to 5% under multiple comparisons.

### Safety analysis

Reported adverse events will be assigned a low-level term (LLT) code using the Medical Dictionary for Regulatory Affairs, Japanese (MedDRA/J). The version of MedDRA/J used for the analysis will be the latest version at the time of database fixation.

Adverse events (TEAEs) observed after protocol treatment initiation will be assessed. Adverse events identified to be causally related to the study drug will be considered side effects.

If an adverse event with the same preferred term (PT) occurred multiple times in one case, the number of occurrences will be considered as the number of events, and the number of cases will be counted separately as one case.

For all adverse events and side effects, the number of occurrences, number of cases, and incidence rate with 95% confidence intervals will be calculated for each treatment group.

The number of events, number of cases, and incidence rate will be determined by system organ class (SOC) and PT classification for each treatment group.

